## Interval Assessments

### Interval history and physical exam

The Procedure of following up both groups EST (every 6 months/24-36 months of follow-u) and CT (as OPC routine procedure according to national guidelines)

- Vital signs and weight
- Physical examination
- Physics development and awareness
- Signs and symptoms of OIs

etc.

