**Study Regions:**

- Hanoi and Ho Chi Minh city

**Study Size:**  Planned enrollment of a total of 540 HIV positive children 10-16 years of age, on ART and randomize to either Enhanced Treatment Support (ETS) or Conventional Treatment (CT).

**Study Duration:** Study enrollment at the second quarter of 2019 and the study will be completed when all patients have completed follow up during 24 months.

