### Interval laboratory test

Patients of 2 groups will be followed for 24 months and monitored every 6 months for viral load. Other laboratory tests schedule as in National guidelines.

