**Peer Support Intervention**

**Follow-up 24 months**

**Analysis**

**Appendix 1 B: Trial Flow Chart for both groups (EST and CT)**

|  |  |  | **24 months follow-up**  **Every 6 months = 6 interval assessment** | | | |
| --- | --- | --- | --- | --- | --- | --- |
| **Event** | **SCR** | **Baseline or enrollment** | **1^st^** | **2^nd^** | **3^rd^** | **4^th^** |
| Informed Consent | x |  |  |  |  |  |
| Inclusion/Exclusion Criteria | x |  |  |  |  |  |
| Medical History | x |  |  |  |  |  |
| Clinical Assessments (vital signs, weight, physical exam) |  | x | x | x | x | x |
| Medication Adherence Assessment (if under ART already) |  | x | x | x | x | x |
| Adverse Event Assessment |  | x | x | x | x | x |
| CBC |  | x | x | x | x | x |
| Liver Enzymes Tests |  | x | x | x | x | x |
| AFB sputum (if available) |  | x | If (indicated) | | | |
| CD4 (if available) |  | x |  |  |  |  |
| Viral load |  | x | x | x | x | x |
| Genotype resistance  (0.5 ml plasma) |  | x | If (indicated) | | | |
| -80 oC Stored plasma  (0.5 ml plasma) |  | x | X | X | x | x |

Volume of Blood sample: 3-4 ml/time, assuming having 1.5 ml of plasma enough for VL, genotypic and storage

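### The arm-specific exam schedule in Interval Assessments contradicts the common 24-month, four-visit chart, so clinical components of the composite endpoint could be detected unequally by arm

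*Protocol*

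**What the plan says.** Four places in the Protocol bear on how long and how often patients are observed.

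- **Interval history and physical exam.** The procedure differs by arm: "EST (every 6 months/24-36 months of follow-u) and CT (as OPC routine procedure according to national guidelines". EST is the intervention arm, called ETS elsewhere. The control arm is given only routine care, with no interval or duration.
- **Interval laboratory test.** "Patients of 2 groups will be followed for 24 months and monitored every 6 months for viral load".
- **Synopsis, Study Duration.** "the study will be completed when all patients have completed follow up during 24 months".
- **Appendix 1 B**, titled "Trial Flow Chart for both groups (EST and CT". It is headed as a 24-month follow-up with "Every 6 months = 6 interval assessment", but it has four follow-up columns, first to fourth. Clinical assessment (vital signs, weight, physical exam) and viral load are marked at baseline and at all four.

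The Evaluation section defines the primary endpoint as time to virological failure and/or death and/or AIDS-associated events (clinical failure). Indicators for Evaluation instead names virological failure alone as primary and makes clinical failure secondary in its text and tertiary in its table. The table measures clinical failure and AIDS events mainly by physical exam.

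**The concern.** A randomised comparison of time to failure needs outcomes to be looked for in the same way in both arms. The exam section and Appendix 1 B cannot both be followed: one gives the arms different exam procedures, the other the same four visits. A site that follows the exam section would examine intervention patients on a fixed study schedule and control patients at whatever interval routine care provides.

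Under the composite endpoint, an exam-based event that is found in one arm and missed in the other enters the primary comparison as a treatment difference. Events that were never recorded cannot be recovered at analysis. The wider duration range and the wrong visit count leave it unclear when follow-up ends.

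**Working it through.** **1. Visit count.** Assessments = follow-up months / interval.
- 24/6 = 4, which matches the four columns of Appendix 1 B.
- 36/6 = 6, which matches the header's figure and the upper end of the range in the exam section.

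The header's six is therefore not reproduced from its own 24 months and six-month interval. The chart is shared, so this slip affects both arms alike.

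**2. Duration.** The 24-month figure appears in the Primary Objectives (up to 24 months), Study Duration, Sample size (failure after 2 years), Interval laboratory test and Appendix 1 B. The rationale for subject selection also depends on it: patients are to reach at most 18 years, and 16 + 2 = 18 whereas 16 + 3 = 19. Only the exam section gives 24-36 months.

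**3. What is observed equally.** Viral load is six-monthly in both arms in Indicators for Evaluation, Interval laboratory test and Appendix 1 B. Conventional adherence assessment is also six-monthly in both arms. The difference by arm is confined to history and physical exam.

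**4. Effect of unequal detection.** The Protocol gives no share of clinical events and no detection rate, so both are assumed. Let c be the share of primary events that are clinical (20% to 40%) and s the fraction of these that routine control care records (50% to 75%). Assume no true effect, with 15% failure at 24 months in both arms (the planning figure for control) and full detection in the intervention arm.

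Observed control failure = 0.15 × (1 − c(1 − s)). Apparent hazard ratio = ln(0.85) / ln(1 − observed control failure).

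| c | s | Observed control failure | Apparent HR, intervention vs control |
|---|---|---|---|
| 0.20 | 0.75 | 14.25% | 1.06 |
| 0.20 | 0.50 | 13.5% | 1.12 |
| 0.40 | 0.75 | 13.5% | 1.12 |
| 0.40 | 0.50 | 12.0% | 1.27 |

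**5. Effect of unequal duration alone.** In 4,000 simulated trials with no true effect, 270 per arm (540/2) and failures detected on a six-month grid, the log-rank test rejected in 4.8% with 36 against 24 months and in 5.6% with 24 months in both arms. Simulation error is about 0.4 points, so there is no sign of bias when follow-up is censored.

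Crude percentages behave differently. At constant hazard (assumed), failure at 36 months = 1 − (1 − p)^1.5, where p is failure at 24 months.
- Intervention: 1 − 0.90^1.5 = 14.6%, against a planned 10%.
- Control: 1 − 0.85^1.5 = 21.6%, against a planned 15%.

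An intervention arm at 36 months set against a control arm at 24 months would show 14.6% versus 15.0%. With no true effect the same mismatch gives 21.6% versus 15.0%, and a two-proportion test with 270 per arm would reject in about 51% of trials. These are hypothetical comparisons; the Protocol states no such pairing.

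**The case against.** The strongest reply is that the Protocol already contains the right design. Appendix 1 B covers both groups and schedules the same clinical assessments, and the laboratory section gives 24 months for both. The longer range is then one stray phrase against a consistent horizon. If virological failure alone is primary, as Indicators for Evaluation says, the key measurement is identical in both arms. The hazard ratios above rest on assumed inputs, and the bias would run against the intervention, so it threatens power rather than creating a false claim of benefit.

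Most of this stands, and it limits the point. It does not remove it: the exam section still instructs sites differently by arm, and the Evaluation section still puts clinical events in the primary endpoint.

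Three stronger readings are tempting and are not supported.
- **That the intervention arm is followed for 36 months and control for 24.** The exam section gives control no duration, and the laboratory section gives both arms 24 months.
- **That unequal duration would bias the time-to-failure comparison.** Survival analysis is planned, and with proper censoring duration alone does not. The exposed results are percentages by arm and logistic regression, both of which the Protocol also plans.
- **That four versus six assessments is a difference between arms.** Both numbers stand in one shared chart. Counting screening and baseline would also make six columns, although the header speaks of six-monthly interval assessments during follow-up.

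**Conclusion.** The point holds as a contradiction in the exam schedule by arm, in the duration and in the visit count. The consequence that matters is possible unequal detection of exam-based clinical and AIDS events under the composite endpoint. Its size cannot be fixed from the Protocol: under the assumed ranges, an apparent hazard ratio of about 1.06 to 1.27 with no true effect. The direction assumes that routine control care records fewer such events than six-monthly study exams. The Protocol does not give the routine interval, so this is a tendency and not a certainty. The virological component is not affected through 24 months. The 14.6% figure applies only to crude percentages, at constant hazard, in a 36-versus-24-month situation that the Protocol does not state.

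**What to change.** - Reconcile Study Duration, Interval history and physical exam, Interval laboratory test and Appendix 1 B to one duration, one assessment count and one assessment schedule, identical in both arms.
- Remove the arm-specific wording from the exam section, so that clinical endpoint components are ascertained at the same Appendix 1 B study visits in both arms.
- Correct the interval-assessment count in the Appendix 1 B header so that it agrees with its columns.
- State that the primary comparison and all percentage outcomes are evaluated at the 24-month horizon already used in the objective and the sample size.

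The cost is Protocol wording. No patients are added, viral load is already six-monthly in both arms, and Appendix 1 B already lists the clinical assessments for both groups.

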### Adherence Intervention and following-up

- Group CT: Adherence assessment and Support as in conventional procedure every 6 months
- Group EST:

- Adherence assessment and Support as in conventional procedure every 6 months

- Additional adherence assessment and Use Peer-Support as in study procedure (peer-support weekly)

### Interval laboratory test

Patients of 2 groups will be followed for 24 months and monitored every 6 months for viral load. Other laboratory tests schedule as in National guidelines.

### Archived plasma for further analysis

Left plasma from routine clinical or research laboratory tests will be stored at -70ºC for further analysis with higher techniques by sending out of Vietnam etc. shared outside the clinical and research team.

# Data Management

Briefly, source documents will be generated during the study by the site study staffs at participating institutions including all recordings of observations or notations of clinical activities, and all reports and records necessary for the evaluation and reconstruction of the clinical trial. Source documents include, but are not limited to, the subject’s medical records, laboratory reports, x-rays, radiologist’s reports, subject’s diaries, biopsy reports, ultrasound photographs, progress notes, pharmacy records, and any other similar reports or records of procedures performed during the subject’s participation in the study.

Access to applicable source documents will need to be made available for study purposes. The site investigators are responsible for maintaining any source documentation related to the study. Source documentation should support the data collected on the online CRF**,** and must be signed and dated by the person recording and/or reviewing the data. Source documentation must be available for review or audit by the sponsor or designee and any applicable national authorities.

Online Case Report Forms (CRFs) will be used as a data collection tool. The study team will transfer the information from the source documents onto the Online CRFs. CRFs may be used as source documents if they are the primary data collection tool for specified data as documented in written standard operating procedures. The site Investigators are responsible for maintaining accurate, complete and up-to-date records and for tracking receipt of CRFs for each participant. These forms are to be completed on an ongoing basis during the course of the study by authorized individuals.

# Monitoring

## Study Monitoring

The trial will be conducted in compliance with this protocol, International Conference on Harmonization (ICH) Guidelines for Good Clinical Practice (GCP) and any applicable regulatory requirement(s).

As per ICH-GCP 5.18 clinical protocols are required to be adequately monitored by the study sponsor. Monitors, research staff and possibly research nurses at the study sites, will visit the clinical research site to monitor all aspects of the study in accordance with the appropriate regulations and the approved protocol. The objectives of a monitoring visit will be: 1) to verify the existence of signed informed consent documents for each monitored subject; 2) to verify the prompt and accurate recording of all monitored data points, and prompt reporting of all unexpected SAEs; 3) to compare abstracted information with individual subjects’ records and source documents (subjects’ charts, laboratory analyses and test results, physicians’ progress notes, nurses’ notes, and any other relevant original subject information); and 4) to ensure protection of study subjects, investigators’ compliance with the protocol, and completeness and accuracy of study records. The monitors also will inspect the clinical site regulatory files to ensure that regulatory requirements (Office for Human Research Protections-OHRP) and applicable guidelines (ICH-GCP) are being followed. During the monitoring visits, the investigator (and/or designee) and other study personnel will be available to discuss the study progress and monitoring visit.

## Data and Safety Monitoring Plan

An independent data and safety monitoring board (DSMB) will oversee the trial. The DSMB will perform interim analyses annually within study period and will be provided with summary tables of selected adverse events and an analysis of mortality.

Based on these data, the committee has to make one of the following recommendations:

- - - Continue the trial without modification
    - Continue the trial with modification
    - Discontinue the trial due to safety concerns

The DSMB may also suggest discontinuation if the trial results indicate “beyond reasonable doubt” that one of the allocated strategies is better than the other in primary outcome.

As the dissemination of preliminary summary data could influence the further conduct of the trial and introduce bias, access to interim data and results will be confidential and strictly limited to the involved statistician and the monitoring board and results (except for the recommendation) will not be communicated to the outside and/or clinical investigators involved in the trial.

# Human Subject Protections

## IRB Approval

This protocol, patient information sheet, informed consent document, relevant supporting information will be submitted to the designated IRB/EC and should be approved before the study is initiated.

Any amendments must also be approved by the designated IRB/EC prior to implementing changes in the study.

## Compliance With Good Clinical Practice

This study will be conducted in compliance with the conditions stipulated by the Ethical Committee of the Viet Nam Ministry of Health as well as International Conference on Harmonisation /Good Clinical Practice standards (ICH/GCP) Guidelines. In addition, all local regulatory requirements will be adhered to, in particular those which afford greater protection to the safety of the trial participants.

## Informed Consent

The informed consent for this study will be translated into Vietnamese and must be signed by the study participant or legal representative before participation in the study, including any screening procedures. A copy of the signed consent must be provided to the study participant. Signed consents must remain in each study participants study file, and be available for verification by study monitors at any time.

In the case of illiterate subjects, the consent will be read in Vietnamese to the subjects.

If the subject is too ill to consent, the next of kin may consent for the subject. Once the subject is able, the subject will be consented for continuation in the study.

## Rationale for Research Subject Selection

### Inclusion of children from 10 - 16 years of age

- The study will only include children from 10 - 18 years of age with 24 months of follow up, during the study they will reach a maximum of 18 years of age and still be under Pediatric OPC management.

### Justification of Exclusion criteria

- The exclusion criteria “Being referred from other sites for temporarily follow-up at site study” is primarily to avoid loss of follow up since they are not under OPC management.
- The exclusion criteria “Institutionalized patients (e.g. orphanage) “ as they have institutional provision of treatment on regular times

## Record Retention

The investigator is responsible for retaining all essential documents listed in the ICH Good Clinical Practice Guideline. All essential documentation for all study subjects are to be maintained by the investigators in a secure storage facility for a minimum of three years. These records are also to be maintained in compliance with IRB/EC retention requirements, whichever is longest. All stored records are to be kept confidential. It is the investigator’s responsibility to retain copies of source documents

## Storage of Samples (if applicable)

Approximately 2 ml of plasma from each visit will be stored in the hospital freezer at -70ºC only for further analysis. Samples and data will be stored using codes (not subjects’ names) assigned by the investigators. Only investigators will have access to the samples and data. At the end of the study, samples will continue to be stored for at least five years in the hospital freezer at -70ºC.

Subjects may decide at any point not to have their samples stored. In this case, the principal investigator will destroy all known remaining samples and report what was done to the subject.

## Anonymity and Confidentiality

The information obtained during the conduct of this clinical study is confidential. The results of the research study may be published, but patient names or identities will not be revealed. Records will remain confidential. To maintain confidentiality, the principal investigators at each site will keep records in locked cabinets and the results of tests will be coded to prevent association with the subject’s names.

**Appendix 1A: Study Flow Diagram**

**Consent**

**Inclusion Criteria**

**Exclusion Criteria**

**Baseline assessment**

**Treatment Randomization (1:1)**

**EST**

**CT**

**Peer Support Intervention**

**Follow-up 24 months**

**Analysis**

**Appendix 1 B: Trial Flow Chart for both groups (EST and CT)**

|  |  |  | **24 months follow-up**  **Every 6 months = 6 interval assessment** | | | |
| --- | --- | --- | --- | --- | --- | --- |
| **Event** | **SCR** | **Baseline or enrollment** | **1^st^** | **2^nd^** | **3^rd^** | **4^th^** |
| Informed Consent | x |  |  |  |  |  |
| Inclusion/Exclusion Criteria | x |  |  |  |  |  |
| Medical History | x |  |  |  |  |  |
| Clinical Assessments (vital signs, weight, physical exam) |  | x | x | x | x | x |
| Medication Adherence Assessment (if under ART already) |  | x | x | x | x | x |
| Adverse Event Assessment |  | x | x | x | x | x |
| CBC |  | x | x | x | x | x |
| Liver Enzymes Tests |  | x | x | x | x | x |
| AFB sputum (if available) |  | x | If (indicated) | | | |
| CD4 (if available) |  | x |  |  |  |  |
| Viral load |  | x | x | x | x | x |
| Genotype resistance  (0.5 ml plasma) |  | x | If (indicated) | | | |
| -80 oC Stored plasma  (0.5 ml plasma) |  | x | X | X | x | x |

Volume of Blood sample: 3-4 ml/time, assuming having 1.5 ml of plasma enough for VL, genotypic and storage

**Questionnaires**

**A. Patient’s demographic characteristics, clinical features and ARV treatment**

The following questions are related to the personal information of the child. Please select the appropriate answer or provide the requested information:

**A1**. Patient’s gender: *☐ 1. Male ☐ 2. Female*

**A2**. Date of birth: _ _/_ _/_ _ _ _ (day – month – year)

**A3.** Province of residence

*☐ 1. Hanoi ☐ 2. Hai Phong ☐ 3. Quang Ninh*

*☐ 4. Ho Chi Minh City ☐ 5. Other provinces*

**A4**. Type of education

*☐ 1. No education*

*☐ 2. Home education*

*☐ 3. Attending school*

*_________________________________*

**B. Family’s demographic and socioeconomic characteristics**

The following questions pertain to the information about the child's family. Please select the appropriate answer or provide the requested information:

**B1.** Number of members in the child's family

*☐ 1. 1 – 2 persons ☐ 2. 3 – 4 persons*

*☐ 3. 5 persons or more*

**B2.** Does the current family have your own house?

*☐ 1. Yes ☐ 2. No*

**B3.** Number of family members living with HIV, excluding children: _____ person

______________________________________________________________

**C. Caregiver’s demographic and socioeconomic characteristics**

The following questions relate to the information about the caregiver. Please select the appropriate answer or provide the corresponding response:

**C1.** Date of birth of the caregiver: _ _/_ _/_ _ _ _( day - month - year))

**C2**. Gender of the caregiver:

*☐ 1. Male ☐ 2. Female*

**C3.** Relationship of the caregiver to the child:

*☐ 1. Mother ☐ 2. Father ☐ 3. Grandmother*

*☐ 4. Grandfather ☐ 5. Others*

**C4.** Education level

*☐ 1. Illiteracy ☐ 2. Basic literacy (able to read and write)*

*☐ 3. Primary school ☐ 4. Secondary school*

*☐ 5. High school ☐ 6. Vocational, college, university of higher*

*☐ 7. Don't know*

**C5.** Primary occupation of the caregiver

*☐ 1. Unemployed ☐ 2. Seasonal work*

*☐ 3. Agriculture ☐ 4. Manual labor*

*☐ 5. Office worker ☐ 6. Business*

*☐ 7. Homemaker ☐ 8. Student*

*☐ 9. Other, specify:______________________________*

**C6.** Average monthly income of the caregiver

*☐ 1. Below 5 million VND ☐ 2. 5 – <10 million VND*

*☐ 3. 10 million VND and above ☐ 4. Not known/No answer*

*______________________________________________________________*

**D. Caregivers’ challenges and supports**

The following questions relate to the difficulties faced by caregivers in caring for children with HIV undergoing ARV treatment, and the support received from family and society. Please select the appropriate answer or provide the corresponding response:

**D1.** Have you ever faced difficulties in caring for patient undergoing ARV treatment?

*☐ 1. Yes ☐ 2. No*

**D2.** Have you received any support from family or friends in caring for patient?

*☐ 1. Yes ☐ 2. No*

**D3.** Have you received any support from the community or society in caring for patient?

*☐ 1. Yes ☐ 2. No*

**D4.** Have you ever felt tired, overwhelmed, or desperate when caring for patient?

*☐ 1. Not at all ☐ 2. Sometimes*

*☐ 3. Always ☐ 4. Don't know/No answer*

*______________________________________________________________*

